## Methods and analysis

### Trial design

This protocol describes the methodology of a parallel-group, two-arm randomized controlled trial, which will employ an intervention condition (CALMA app) and a control condition (Treatment as usual-TAU) with a 3-month follow-up for each participant. Participants will be assessed at four timepoints: day-0 (baseline), day-30, day-60, and day-90.

The intervention group will receive the CALMA app and continue with the usual treatment in a public hospital mental health service. The CALMA app will be downloaded with the assistance of a team member into the participant’s smartphone during the first interview. In each follow-up interview (30-days and 60-days), the use of the app will be reinforced. The control group (TAU) will not receive the app but will keep doing the usual treatment provided in public hospitals throughout the study. The usual treatment in public hospitals in Argentina consists of a weekly visit to a psychologist and a monthly visit to a psychiatrist (in case the patient receives any pharmacological treatment). In the public hospitals of Argentina, there are no DBT programs, and most of the interventions are psychoanalytic.

### Study setting

Young people aged 10 to 19 years (WHO definition of adolescence) who attend a Mental Health Services of the Pedro de Elizalde Children’s General Hospital (in the City of Buenos Aires), and the Children’s Hospital “Sor María Ludovica” from the city of La Plata (Province of Buenos Aires) who have presented some type of self-injurious behavior (with or without suicidal intent) the month before the evaluation will be randomly assigned to one of the arms of study.

### Patient eligibility

#### Subjects

Patients aged 10 to 19 who attend on as outpatient basis or have been hospitalized in Mental Health Services and who have a smartphone where the application can be installed and used are eligible to participate in the study. In addition, participants must have had suicidal behavior in the 4 weeks before entering the study. The SITBI assessment questions will be used to define suicidal behavior: suicide attempt [“made a suicide attempt (i.e., purposefully hurt yourself with at least some intent to die)?”], exhibited a suicidal gesture (Have you ever done something to lead someone to believe that you wanted to kill yourself when you really had no intention of doing so?) or self-injurious behavior (Have you ever done something with the purpose of hurting yourself without wanting to die?–for example, cutting or burning-) in the last month before entering the study (53, 54).

The participant must have plans to continue treatment in the next 3 months, have the ability to provide assent/consent for cognitive or language reasons, and the functional capacity to use the application, which will be operationally determined by a score above 30 on the Self-Care motor domain, above 10 on the Communication cognitive domain and above 14 on the Cognitive domain of Social Knowledge in the Functional Independence Measurement scale (46).

### Intervention

#### Implementation of the intervention

CALMA is an app for smartphones that interacts with the user, providing evidence-based tools to prevent suicide; it is openly available and free to download on Apple or Google market place. It was developed, with contribution of mental health professionals, by our research group which are also mental health professionals. CALMA is based on the DBT program, which is one of the third-wave cognitive-behavioral therapies and seeks to train consultants with self-injurious behavior with and without suicidal intent in emotional regulation skills in order to manage their emotions more effectively (13, 55). CALMA integrates DBT strategies in two modalities: “Out of crisis” in which the user has some vulnerability reduction strategies to reduce the probability of crisis appearance, and the “I Need Help” modality (aimed at helping the user in crisis) constituted first with problem-solving strategies (DBT always gives the opportunity to solve the problem that triggered the crisis) and then, if the intensity of the crisis does not decrease, it implements distress tolerance or emotional regulation DBT skills dependent on the level of distress rated by the user (concept derived from the *breaking point* of DBT skills). A detailed description of the development of CALMA has been described elsewhere (51). All the features of CALMA app are based on face-to-face interventions that have shown efficacy in the reduction of self-injurious behavior and that are part of the central axis of the DBT program such as problem-solving (54), emotion regulation (13, 55, 56), distress tolerance (13, 55, 56) and also access to emergency contacts at the time of the crisis (31, 35). The app offers these interventions sequentially, and users can select which to employ. To guarantee the fidelity of the CALMA app to the model, DBT therapists have been included as stakeholders in the design of the intervention. Also, participants’ opinion was considered (52). In the management of an emotional crisis, the CALMA app follows the steps of crisis management and telephone coaching, initially going through the problem-solving strategy until reaching discomfort tolerance or emotional regulation skills as self-management strategies (11, 57, 58). The “Out of Crisis” modality consists of four functions that are identified in the initial screen of the app (Figure 1). The “Moments” function is based on the Inventory of Reasons to Live (59), considering that reasons for living reduce the risk of suicide (59, 60). In “Moments,” the user can add photos, videos, audios, songs, phrases, or anything that generates well-being and works as an anchor to life. The (b) “Agenda” function is based on evidence that positive events, such as pleasurable activities, serves as a protective factor for SI, thus reducing vulnerability to future suicidal crises (61). Moreover, engagement in positive events serves as a buffer between stressful adverse events and SI (62). The (c) “Profile” function provides the option for the user to add names and telephone numbers of people who can be contacted during a crisis if the crisis is not able to be resolved with the “Emergency Card” (see later). The (d) “Tips” function provides psychoeducational material related to suicidal crises and how to prevent unwanted behaviors during these crises. The user receives a weekly notification as a reminder of these sections. The “I need help” modality consists of interventions based on DBT skills. The skills were designed to be easily accessed during a crisis by the user activating the “I need help” button at the bottom of the home screen. All interventions are presented in a card format.

**Figure 1 fig1:**
[figure not shown]
Functions of “Out of Crisis” mode of CALMA: Moments, Agenda, Profile and Tips.

The “Problem-solving Card” is the first card presented and helps the user evaluate if the problem that triggered the crisis can be addressed using problem-solving (Figure 2), which is an effective strategy for people experiencing SI and SA (63–66). If the problem cannot be addressed using problem solving, the next step is to use the “CALMA thermometer” and “DBT Skills Cards.” The “CALMA thermometer” allows the user to identify what emotion he or she is feeling and to quantify the intensity of the emotion using a 10-point thermometer (Figure 3).

**Figure 2 fig2:**
[figure not shown]
“I need help” mode of CALMA: Problem-solving Card.

**Figure 3 fig3:**
[figure not shown]
“I need help” mode: CALMA thermometer.

“DBT Skill Cards”: CALMA includes different cards with DBT skills (interventions) to manage emotional crises (Figure 4). Each card provides a specific DBT skill and the instruction on how to do it. The user can read, view, or listen to the content of each card and choose to perform the skill or discard it. The DBT Skill Cards are based fundamentally in two groups of DBT skills, emotional regulation and distress tolerance. Once the skill is applied, the user must re-score the intensity of the emotion via the CALMA thermometer. According to the effectiveness of the intervention, the app follows an algorithm designed to select the next card that the user will receive.

**Figure 4 fig4:**
[figure not shown]
“I need help” mode of CALMA: DBT Skills Cards.

“Emergency Card”: if distress worsens or does not diminish after three attempts, CALMA activates the “Emergency Card” (Figure 5). This card offers the user the option to make one or several calls emergency contacts previously loaded or standardized emergency numbers (e.g., 911). This card also provides the user the option to use the geolocation function, which uses Google Maps to show all emergency services near the user’s location so that he/she can consult personally.

**Figure 5 fig5:**
[figure not shown]
“I need help” mode of CALMA: Emergency Card.

The CALMA version used for this trial is identical to the one available for download.

This app was initially developed to be used by a mental health clinician as a complement to psychological and psychopharmacological treatments, but it can also be used by individuals who do not have access to the health system or who are afraid of being stigmatized, since it does not require training for its use and all the information is contained in the same app. The intervention was based on DBT’s biosocial theory and on the principles of learning that posits that the patient lacks skills to manage painful emotions. CALMA offers the possibility of putting these emotional regulation skills into practice, with instructions on how to carry them out, increasing the probability of incorporating these behaviors into the user’s behavioral repertoire through validation and/or reinforcement phrases as appropriate. In addition, before proposing skills, CALMA promotes the use of problem-solving strategies in each of the crises. The increase in perceived self-efficacy in crisis resolution and the learning of DBT skills can help the patient become less involved in behaviors related to suicide, through the increase in the ability to regulate emotionally as a mediator of the effect. CALMA also works between crisis situations by promoting activities aimed at reducing the subject’s vulnerability to emotional crises and providing psychoeducational content about suicide and its prevention.

The intervention includes different behavior change techniques such as problem solving (1.2.), reducing negative emotions (11.2.), distraction (12.4.), shaping knowledge (i.e., instruction on how to perform the behavior) (4.1.), non-specific reward (10.3.) and social support (unspecified) (3.1) from the BCT Taxonomy v1 (67).

Finally, CALMA complies with the current system and privacy recommendations for the design of mobile applications for suicide prevention (49).

### Outcomes measures

#### Primary outcome measure

Suicidal behavior will be assessed using the Spanish version of the Self-Injurious Thoughts and Behaviors Interview (SITBI) (68, 69). This is a structured interview consisting of 169 items divided into 5 modules that examine the presence, frequency and characteristics of 5 types of self-injurious behavior: (a) suicidal ideation; (b) suicide plans; (c) suicidal gestures; (d) suicide attempts and (e) self-harm. The SITBI conceptualizes suicide risk on a continuum, starting with suicidal ideation (“thoughts of killing yourself?”), possibly accompanied by a suicide plan [“think about how you might kill yourself (e.g., taking pills, shooting yourself) or work out a plan of how to kill yourself?”] and in some cases by suicide attempt [“made a suicide attempt (i.e., purposefully hurt yourself with at least some intent to die)?”]. The construction of the questions in the original SITBI is consistent with the commonly accepted definitions of each type of behavior. The administration of the scale takes between 3 and 15 min.

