The evidence on the efficacy and effectiveness of suicide prevention strategies, such as Dialectical Behavioral Therapy (DBT), have been described (11–14). Indeed, DBT prioritizes suicidal behavior as the primary goal of treatment. In a meta-analysis of 18 RCTs, DeCou et al. demonstrated a significant pooled effect for DBT compared to control groups for self-directed violence (suicidal and NSSI behavior; *d* = −0.324, 95% CI = −0.471 to −0.176); however, there was no significant pooled effect of DBT for suicidal ideation (15). A more recent review, which evaluated the benefits and harms of psychological therapies for borderline personality disorder, identified DBT as having the largest number of primary trials, finding it to be the most effective psychotherapy at reducing self-harm (SMD-0.28, 95% CI-0.48 to-0.7; 7 trials, 376 participants) compared to TAU (16). Furthermore, in adolescents, 19 weeks of DBT was associated with a significantly lower frequency of self-harm episodes and suicidal ideation at post-treatment, 1 year, and 3 years follow-up (17, 18). In addition, some studies with similar results have added data regarding the feasibility of implementing DBT in adolescents, even at a community level, a necessary hallmark of the program (19, 20). Recently, a meta-analysis by Witt et al. concluded that there was a lower recurrence rate of self-harm (intentional self-harm) for adolescent DBT (30%) compared with treatment as usual, enhanced usual care, or alternative psychotherapy (43%) in repeated post-intervention self-harm in four trials (OR 0.46, 95% CI 0.26 to 0.82; *N* = 270; *k* = 4; high-certainty evidence) (21).

Despite this, and due to the short time to intervene in the suicidal process (22, 23), a crucial aspect of their effectiveness in daily practice is accessibility. This is why, beyond employing effective interventions to prevent suicide, they must be quickly available at the time of crisis.

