## Objectives

### General objective

To evaluate the efficacy, safety and acceptability of CALMA, a suicide prevention app for smartphones, to reduce the frequency of self-injurious thoughts and behaviors in adolescents who are assisted in a Mental Health service at two Public hospitals.

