### Specific objectives

#### Primary specific objectives

Compare the change in the frequency of self-injurious behaviors in the participants who receive the app with the frequency in those who do not receive the application.

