#### Secondary specific objectives

Analyze the frequency of self-injurious thoughts in the participants who receive the application with the frequency in those who do not receive the app.Establish that there is no increase in the frequency of self-injurious thoughts and behaviors in those participants who receive the application compared to the baseline levels at study onset.To explore whether the effectiveness of CALMA in reducing the frequency of self-injurious thoughts and behaviors is mediated by improved emotional regulation.Describe the levels of app engagement by the adolescent participants who used it during this study.To compare the time to psychiatric admission during the follow-up period in the participants enrolled who received the app with those participants who did not receive the app.

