### Statistical analysis

To describe the sociodemographic characteristics of the patients in the two groups, absolute and relative frequencies (%) will be used for the qualitative variables, and the mean and standard deviation will be used for the only quantitative variable (age) if it presents a normal distribution according to the Shapiro–Wilk test. In case of presenting a non-normal distribution, the median and the interquartile range will be computed.

To compare the sociodemographic characteristics between the groups, the chi-square or Fisher’s exact test will be used for the qualitative variables, and the student’s t-test or the Mann–Whitney U test will be computed for the quantitative variable.

For all patients and at each follow-up moments, the difference between the frequency of each suicidal behavior and the baseline frequency will be calculated. Then it will be evaluated if these differences follow a normal distribution (Shapiro–Wilk test). In this case, the mean differences for each behavior between both groups will be compared using the t-Student test. Otherwise, the medians will be compared with the Mann–Whitney U test. The *p*-values obtained will be corrected according to the Bonferroni criterion.

To assess whether the change in emotional regulation mediates the change in the frequencies of each suicidal behavior, the difference between the value of the DERS scale at the last follow-up and the baseline will be calculated, and the Sobel test will be used on a regression model whose dependent variable will be the difference in the frequency of each behavior and the independent variable will be the treatment. Previously, the probability distribution of the quantitative variables will be evaluated and it will be considered whether it is necessary to carry out any transformation of data to guarantee compliance with the assumptions of the regression model.

Both for the frequencies of the different suicidal behaviors and for the DERS scale, the missing values will be imputed according with the multiple imputation method using chained equations (MICE) with appropriate models for each variable to be imputed, considering sociodemographic characteristics, the hospital of recruitment and the baseline measurements of frequencies and DERS scale as independent variables.

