In a prior pilot study, the CALMA app has shown initial evidence of safety and acceptability of the app for reducing self-injurious thoughts and behaviors when used as an adjunct to conventional DBT therapy within 4 weeks of follow-up (52). This study has shown good acceptability of CALMA as an adjunct to therapy targeting suicidal and non-suicidal self-injured behaviors. Furthermore, a high probability of decreased in SI, suicidal plan, suicidal gesture, thoughts about Non-Suicidal Self-Injury (NSSI) and NSSI pre-and post-intervention was observed in the group that received CALMA and a high probability of a greater decrease in SI and suicidal gesture before and after the intervention for the group that received CALMA compared to the comparison group.

This protocol describes a parallel-arm randomized controlled trial, which aims to test the efficacy, safety and acceptability of the CALMA application as an adjunct to therapy to reduce suicidal and non-suicidal self-injurious behaviors in adolescents.

This research will fill important gaps about the engagement and effectiveness of a DBT skills-based application in adolescents. Firstly, there are few studies of apps that focus on adolescents with suicidal behaviors, a population at higher risk of suicide and with distinctive characteristics (80); only some have the characteristic of being interactive with the user. Second, of the few studies that did measure effectiveness in this population, the results were negative. Third, this study is particularly relevant to young people given their widespread use of mobile technology, while there are currently no available mobile applications in Spanish at all that attempt to reduce suicidal behavior in this population (35, 81). Fourth, having a tool that can help reduce the probability of hospitalization for suicidal behavior that is economical, universal, and that is at the service of the crisis, such as an application, would undoubtedly democratize access to specific and effective intervention. Fifth, if the exploratory objective of this study demonstrates that the reduction of self-injurious behaviors is mediated by the improvement of emotional regulation, an app such as CALMA can be an invaluable tool to increase the capacity (skills) to manage intense and painful emotions.

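### The primary outcome can be read as three or five SITBI modules, because suicidal ideation and plans are listed under it while the objectives make thoughts secondary

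*Protocol article*

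**What the plan says.** All references are to the protocol article.

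- **General objective:** thoughts and behaviours are taken together; the app is meant "to reduce the frequency of self-injurious thoughts and behaviors in adolescents".
- **Primary specific objectives:** behaviours only: "Compare the change in the frequency of self-injurious behaviors in the participants who receive the app", against those who do not receive it.
- **Secondary specific objectives:** thoughts are placed here: "Analyze the frequency of self-injurious thoughts in the participants who receive the application".
- **Subjects (eligibility):** "The SITBI assessment questions will be used to define suicidal behavior: suicide attempt", followed by suicidal gesture and self-injury. Ideation and plans are not in this definition.
- **Primary outcome measure:** suicidal behaviour is assessed with the SITBI, whose five modules are described as five "types of self-injurious behavior: (a) suicidal ideation; (b) suicide plans; (c) suicidal gestures; (d) suicide attempts and (e) self-harm". No module is named as primary or excluded.
- **Secondary outcome measures:** emotional dysregulation (DERS), engagement with the app and time to psychiatric admission. Ideation and plans do not appear.
- **Sample size:** 25 per group for one two-sided Mann–Whitney comparison of self-injurious behaviours at d = 0.85.
- **Statistical analysis:** at each follow-up, "the difference between the frequency of each suicidal behavior and the baseline frequency will be calculated" and compared between groups, with Bonferroni-corrected p-values. The size of the family is not given, and thoughts are not separated from behaviours.

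**The concern.** Two of the five SITBI modules, ideation and plans, measure thoughts. The only section that defines the primary outcome calls them types of behaviour, and no other outcome section takes them up. The objectives treat thoughts as secondary. What the trial may claim then depends on which section is followed.

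If the primary outcome section governs, ideation and plans are primary comparisons and share the primary correction. A trial that shifts only those modules could be reported as positive on its primary outcome while its primary objective, fewer self-injurious behaviours, is not met. If the eligibility definition governs, such a trial is negative on its primary outcome and has a secondary finding. The choice should be fixed in the text before anyone sees results.

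The background section shows that the two kinds of outcome need not move together. In the meta-analysis of DBT trials cited there, self-directed violence fell but "there was no significant pooled effect of DBT for suicidal ideation".

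**Working it through.** **1. Which modules does each section point to?**

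- Behaviours only: the primary specific objective, the eligibility definition (attempt, gesture, self-injury), the sample size and the outcome sentence in the abstract.
- All five modules: the description under Primary outcome measure, read as it stands.
- Undetermined: Statistical analysis. Its term for each suicidal behaviour means three modules under the eligibility definition and five under the primary outcome description.

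The secondary outcome list does not settle it, because ideation and plans are not on it. The only outcome heading they sit under is the primary one.

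**2. The plan's own sample size.**

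Inputs from Sample size: d = 0.85, two-sided 0.05, power 80%, Mann–Whitney U. Method: noncentral t with the sample size multiplied by the asymptotic relative efficiency (ARE) of the test, taken as 3/π for a normal parent (an assumption).

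- Effective n per arm = 25 × 3/π = 23.87
- Noncentrality = 0.85 × √(23.87/2) = 2.94, with 2 × 23.87 − 2 = 45.7 degrees of freedom
- Power at 0.05 = 0.82
- Smallest n for 80% power: 24 per arm with ARE 3/π, or 27 with the minimum ARE of 0.864

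The stated 25 lies between these, so it reproduces for **one** comparison at 0.05. The stated 29 follows from 25 × 1.15 = 28.75.

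**3. What the reading does to the correction.**

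The family size is not stated, so both plausible cases are shown. Power is for one behaviour at 25 per arm and d = 0.85, by the same method.

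| Visits counted | Behaviours only | All five modules | Difference |
|---|---|---|---|
| One | 0.05/3 = 0.0167, power 0.67 | 0.05/5 = 0.0100, power 0.60 | 0.07 |
| Three (days 30, 60, 90) | 0.05/9 = 0.0056, power 0.52 | 0.05/15 = 0.0033, power 0.45 | 0.07 |

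Adding the two thought modules costs about 7 percentage points either way. With three visits, the larger fall, from 0.82 to 0.52 (30 points), comes from testing several behaviours at several visits and would remain with thoughts excluded.

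**The case against.** The list of five types describes the interview, not the endpoint. The sentence that names the outcome speaks only of suicidal behaviour, and the eligibility section uses SITBI questions to define that term without ideation or plans. The abstract, the primary objective and the sample size agree. Much of this stands: the weight of the text favours a behaviours-only primary outcome. It does not remove the ambiguity, because the section that should fix the outcome labels thoughts as behaviour, sets no restriction, and leaves ideation and plans with no other place among the outcomes.

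A condensed article may also leave the detailed analysis of a secondary objective to an analysis plan. That stands too. A reader might infer that thoughts have no planned analysis; the article alone does not support that. Which constructs are primary, however, is fixed in the article itself, and there its sections disagree.

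Bonferroni correction is a weaker defence. It limits false positives, but it does not stop a true effect on thoughts alone from being counted as primary.

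Two stronger readings go too far.

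- **That the cited evidence predicts an effect on thoughts without one on behaviours.** The meta-analysis diverged in the opposite direction, and the same section reports that DBT in adolescents was associated with less self-harm and less ideation. The pilot showed "a high probability of a greater decrease in SI and suicidal gesture before and after the intervention for the group that received CALMA", and gesture is a behaviour. The evidence shows that divergence is possible, not that it is likely in this direction.
- **That a misleading positive result has a known, high probability.** A simulation with 25 per arm, a thoughts effect of d = 0.85 at all three visits and no effect on behaviours gives at least one significant result among 15 corrected tests in about 86% of trials at correlation 0.5 (71% to 98% for correlations from 0.8 to 0). It gives about 4% with nine behaviour tests. At d = 0.5 the 86% becomes 35%. These figures are illustrative only. The protocol gives d = 0.85 for behaviours, not thoughts, and nowhere says that any one significant test makes the trial positive.

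**Conclusion.** The concern holds as an internal inconsistency. The primary outcome can be read as three or five SITBI modules, and on the five-module reading a result significant only for ideation or plans could be reported as a primary success that the primary objective does not support. This rests on the text alone and needs no assumption about effect sizes.

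The calculable cost is modest: about 7 points of power for one behaviour (0.52 to 0.45 if all three visits are counted). It assumes 25 evaluable per arm, d = 0.85, Mann–Whitney tests with a normal parent, and Bonferroni correction over modules and visits. The documents do not support attaching a probability to a misleading positive result.

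Narrowing the modules does not settle the primary conclusion by itself. Three behaviours at three visits still leave nine tests, with no stated rule for which result decides.

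**What to change.** - **Primary outcome measure:** define the primary outcome as change in frequency on the SITBI suicidal gesture, suicide attempt and self-harm modules, the three behaviours already used for entry.
- **Secondary outcome measures:** add the ideation and plan modules, in line with the secondary objective.
- **Statistical analysis:** limit the primary Bonferroni family to the behaviour comparisons and give its size. State which follow-up visit or visits, and which result, decide the primary conclusion. Analyse ideation and plans as a separate secondary family that cannot by itself support a positive primary conclusion.

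The cost is wording in three sections, with no new data and no additional participants. The downside is that an effect on ideation alone could be claimed only as a secondary result. The change should be made and dated before outcome data are seen by arm.
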